#### **7.5.3 Measures after permanent discontinuation**

The investigators should provide follow-up medical care for all patients who are permanently discontinued from the study, and should inquire the cause of drug withdrawal, presence of the primary outcomes and adverse events in detail. Besides, investigators should follow up on primary outcomes and adverse events and record in the CRF. Investigators should recall the remaining unused study drugs.

Patients discontinuing from study drugs before the last visit should accomplish the 90-day follow up as planned or when recovered from adverse events to normal/stable condition (the later time point should be chosen). Investigators should document all definite withdrawal carefully in the CRF.

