### 2.2 Secondary purposes:

**2.2.1** To evaluate the efficacy of intensive antiplatelet therapy versus standard antiplatelet therapy, immediate intensive statin therapy (atorvastatin 80mg/d) versus delayed intensive statin therapy

(atorvastatin 40mg/d), intensive antiplatelet therapy combined with immediate intensive statin therapy (atorvastatin 80mg/d) versus standard antiplatelet therapy combined with delayed intensive statin therapy respectively (atorvastatin 40mg/d) at 90 days in acute mild ischemic stroke or high-risk TIA patients attributed to intracranial or extracranial atherosclerosis on the incidence of (definitions shown in appendix 1, 2 and 5):

- Combined vascular events: stroke (ischemic or hemorrhagic), myocardial infarction, and cardiovascular death.
- Ischemic stroke
- TIA
- Severity of stroke or TIA on an ordinal scale: a six-level ordered category scale combined vascular events with mRS score at 90 days: fatal stroke (stroke with subsequent death), severe stroke (stroke followed by mRS of 4-5), moderate stroke (stroke followed by mRS of 2-3), mild stroke (stroke followed by mRS of 0-1), TIA, and no stroke/TIA
- Myocardial infarction
- Vascular death
- All-cause death
- Poor functional outcome (mRS score 2-6)
- Poor quality of life (EQ-5D scale index score  $\leq 0.5$ )

**2.2.2** To evaluate the efficacy in decreasing early neurological deficits (increase in NIHSS score at 7days), stroke recurrence, all-cause mortality and poor functional outcome (mRS score 2-6) at 1 year of intensive antiplatelet therapy versus standard antiplatelet therapy, immediate intensive statin therapy (atorvastatin 80mg/d) versus delayed intensive statin therapy (atorvastatin 40mg/d), intensive antiplatelet therapy combined with immediate intensive statin therapy (atorvastatin 80mg/d) versus standard antiplatelet therapy combined with delayed intensive statin therapy (atorvastatin 40mg/d) respectively in acute mild ischemic stroke or high-risk TIA patients attributed to intracranial or extracranial atherosclerosis. The new stroke or TIA is classified on a six-level ordered category scale combined vascular events with mRS score at 1 year: fatal stroke (stroke with subsequent death), severe stroke (stroke followed by mRS of 4-5), moderate stroke (stroke followed by mRS of 2-3), mild stroke (stroke followed by mRS of 0-1), TIA, and no stroke/TIA.

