#### **7.5 Temporary, permanent discontinuation of the study drug(s) or loss to follow-up**

Study drug should be maintained as long as possible. Judgment for temporary discontinuation should be made when facing withdrawal. Permanent discontinuation is the last resort. Any forms of discontinuation of the study drug should be documented in CRF in detail. Subjects should participate in the study as long as possible in any situations. After randomization, study drug discontinuation for any reason does not constitute withdrawal from the study or stopping follow-up, evaluation and visit should be continued.

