#### **7.5.2 Discontinuation from the study drug permanently**

- 1) Patient's decision. Patients can discontinue the study anytime they want unless it will affect their treatment.
- 2) Investigator's decision. Including but not limited to the following circumstances:
  - h) Primary outcomes (ischemic or hemorrhage stroke) occur
  - i) Pregnancy or preparation for pregnancy
  - j) Incorrect enrollment that does not meet the inclusion/exclusion criteria puts the patient at higher risk
  - k) Serious noncompliance
  - l) Emergence of adverse events that investigators believe may put patients at higher risk of continuing treatment
  - m) Definite indications for anticoagulant agent
  - n) Investigators decide it is inappropriate to restart the study drug after discontinuation

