#### **7.6 Quit from study**

Those who quit the study should not be included again. The randomization number and study drugs of this subject should not be used again. Randomized patients must not be replaced. Investigators should confirm the withdrawal along with the monitoring committee. Subjects who were randomized and had one or more doses recorded were required to complete the calendar visits according to the protocol.

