#### **10.5 Day $90 \pm 7$ visit**

- Finish clinical scores (NIHSS, mRS, EQ-5D).
- Finish intracranial arterial high-resolution MRI (only for high resolution MRI subgroups).
- Finish laboratory tests: blood routine and biochemical panel (including liver function, renal function, blood lipids, creatine kinase). Fasting venous blood sample should be collected at the same time, and serum, plasma and white blood cells should be extracted and stored separately (Instructions are listed in the biological sample collection handbook).
- Record concurrent medication since last visit.
- Evaluate the compliance of the subject since the last visit.
- Record new strokes and new vascular events since the last visit.
- Record adverse events, bleeding events since the last visit.
- Retrieve study drug box of phase 2 (Study drug from day  $22 \pm 2$  to day 90).
- Summarize the whole study.
- The subject and the investigator decide which anti-platelet drug should be used after the study together.
- Inform the subject for long-term follow-up, make an appointment of the next visit: 12th month  $\pm$  14 days after administration.

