## 15. Safety Monitoring of Data

Corresponding data security monitoring plan will be developed based on the risk of the Clinical Trial. All adverse events will be recorded in detail, properly handled and tracked until events are resolved properly or the condition becomes stable. Serious adverse events and other events should be reported to the ethics committee, competent authorities, sponsors, and drug supervision and management departments according to applicable regulations. The main investigators will regularly review all adverse events. Researchers meeting will be held to assess the risks and benefits of the study if necessary. For studies that exceeds the minimum risk, independent data monitor will be assigned to monitor the research data. An independent data safety inspection committee will be established for high-risk research to monitor the accumulated safety data and effectiveness, making recommendations on whether to proceed with the proposal or not.

During the clinical trial, the subject's data should be collected anonymously on the CRFs. Subjects can only be identified as the subject number and the “pinyin” abbreviation of name. Due to security or administrative instructions, those who accidentally knows the identity of the subject should be responsible for confidentiality along with the investigators. Informed Consent Forms allow authorized sponsors, ethical committees, and authoritative agencies to directly access relevant original data on CRFs (such as patient medical records, appointment records, original laboratory records, etc.). The above personnel should follow the professional secrecy regulations and must keep confidential data of patients’ personally identifiable information or medical information.

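### Section 7.5.3, as literally worded, lets the 90-day assessment of patients who permanently stopped study drug wait for recovery or stabilisation, in conflict with the calendar-visit rules

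*Supplement*

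**What the plan says.** All references are to protocol V4.0, the latest version in the supplement.

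- **Section 7.5.3** says patients who stop study drug early "should accomplish the 90-day follow up as planned or when recovered from adverse events to normal/stable condition (the later time point should be chosen"). It sets no latest date.
- **Section 7.5.2** lists the grounds for permanent discontinuation. One, at the investigator's decision, is "Primary outcomes (ischemic or hemorrhage stroke) occur". Others are adverse events judged to raise risk, serious noncompliance, pregnancy, wrong enrolment, an indication for anticoagulants, and the patient's own choice.
- **Section 7.5** says "study drug discontinuation for any reason does not constitute withdrawal from the study or stopping follow-up, evaluation and visit should be continued".
- **Section 7.6** says randomised patients with at least one recorded dose "were required to complete the calendar visits according to the protocol".
- **Sections 3.2 and 10.5** place the visit at Day 90±7 and make no exception for patients off drug. NIHSS, mRS, EQ-5D and the liver and CK panel are taken then.
- **Section 2.2.1** defines the severity outcome as "a six-level ordered category scale combined vascular events with mRS score at 90 days".
- **Section 15** already requires all adverse events to be "tracked until events are resolved properly or the condition becomes stable".

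**The concern.** An assessment date should not depend on what happens to the patient after randomisation. Patients seen after an event has settled will tend to score better than they would have at Day 90. If one arm has more patients waiting for recovery, more of its poor scores are softened and the between-arm difference shrinks.

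The outcomes at stake are secondary: mRS 2-6, EQ-5D ≤0.5 and the six-level severity scale. The procedure table in Section 10.9 schedules mRS and EQ-5D only at baseline, Day 90 and Month 12. No other scheduled score can stand in for a Day 90 value taken late. Section 16.3.1 allows last observation carried forward, and for these two scales the last scheduled earlier value is the baseline one.

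**Working it through.** **Side-by-side reading**

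1. The object of the sentence in 7.5.3 is the 90-day follow-up itself. It joins two times with an *or* and tells the site to take the later one. Literally, that selects a single date.
2. Sections 7.5 and 7.6 say stopping drug does not change the visits. Sections 3.2 and 10.5 fix the window, and 2.2.1 names 90 days for the mRS. A visit delayed under 7.5.3 beyond Day 97 breaks all of these.
3. Section 16.3.1 names exceeding the follow-up window as a possible serious violation for the per-protocol set. A site that obeys 7.5.3 can therefore create a per-protocol violation.
4. The delay applies only to a patient who has permanently stopped drug **and** whose adverse event is neither recovered nor stable at Day 90. Because stable is enough, a patient with a fixed deficit is still seen on time.
5. Section 7.5.3 names primary outcomes and adverse events separately, as does 7.5.2. Section 10.8.2 exempts events resulting from recurrent ischaemic stroke from serious adverse event reporting. Whether a recurrent stroke alone triggers the delay is therefore unclear.

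**Sizing**

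The inputs come from Table 2 of Section 16.1: stroke risk 0.1157 (control) and 0.0930 (treatment), with 2896 per arm after losses.

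The plan's own figure, by the two-sided normal approximation at α = 0.05:

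- Pooled risk = (0.0930 + 0.1157)/2 = 0.10435.
- Null standard error = √(2 × 0.10435 × 0.89565/2896) = 0.008034.
- Alternative standard error = √((0.0930 × 0.9070 + 0.1157 × 0.8843)/2896) = 0.008028.
- z = (0.0227 − 1.96 × 0.008034)/0.008028 = 0.866, so power = 0.8068. The plan states 0.807, so it is reproduced.

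Expected strokes: 2896 × 0.1157 = 335 and 2896 × 0.0930 = 269, about 604 in all. The gap in stroke risk is 2.27 percentage points.

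Assumptions not in the documents:

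- Every stroke leads to permanent stop and counts as a trigger.
- A share f = 5-30% of these patients is neither recovered nor stable at Day 90.
- A share q = 10-50% of the delayed patients crosses the mRS 2-6 threshold because of the delay.
- f and q are the same in both arms.

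| | f = 5%, q = 10% | f = 30%, q = 50% |
|---|---|---|
| Assessed late (604 × f) | 30 | 181 |
| Reclassified, control (335 × f × q) | 1.7 | 50.3 |
| Reclassified, treatment (269 × f × q) | 1.3 | 40.4 |
| Between-arm shift (2.27 points × f × q) | 0.01 points | 0.34 points |

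The shift is towards no difference. The plan gives no expected rate for mRS 2-6, EQ-5D ≤0.5 or non-stroke discontinuations, so the bias relative to those outcomes, and the part due to other adverse events, cannot be sized.

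**The case against.** The best defence is that 7.5.3 sets only a minimum length of safety follow-up: to Day 90, or longer if an adverse event is still open. The neighbouring sentences concern follow-up of outcomes and adverse events, and the calendar-visit passages can be taken as the intended rule. On that reading nothing moves. This stands as a possible reading, but the sentence does not say it, and sites could reasonably act on either.

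Three stronger inferences are tempting, and the documents do not support them.

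- **That exactly the patients with events are scored late.** The rule covers everyone who permanently stops, including for noncompliance or by choice, and omits patients with events who stay on drug. At most, the group is enriched for events.
- **That many recurrent strokes will be graded too mild.** That treats stroke as a clear trigger, which the text leaves open, and needs shares the documents do not give.
- **That liver or muscle toxicity is hidden.** Section 4.4 defines these by occurrence, so a late normal panel does not erase a recorded abnormality. Section 10.5 records adverse events since the last visit, and a transaminase rise above twice normal falls under temporary interruption (7.5.1), to which 7.5.3 does not apply. One gap remains. Section 10.3 waives the Day 7 panel if tests were done within 24 hours of screening or randomisation, so an abnormality never sampled before a delayed visit could be missed.

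It is also fair that handling of out-of-window values is usually SAP material. Section 16.3 defers detail to an SAP that is not shown, so its absence here is no fault.

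**Conclusion.** The point holds as a conflict of wording with a limited consequence. Taken literally, 7.5.3 makes the timing of three secondary outcomes depend on post-randomisation course, and nothing ranks it against the passages that say otherwise. That conclusion needs no assumption.

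The size does. The 0.01-0.34 point range for mRS 2-6 is illustrative and rests on the four assumptions listed with it. If a stroke alone does not trigger the delay, the stroke contribution disappears and only other adverse events remain. The primary analysis of time to first stroke does not use the date of the mRS and EQ-5D visit. The change is still worth making, because the bias is systematic and avoidable, and Section 15 already provides the safety follow-up that the sentence may have been meant to secure.

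**What to change.** Reconcile 7.5.3 with Sections 7.5, 7.6, 3.2, 10.5 and 2.2.1:

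- Every randomised patient has the Day 90±7 assessments (endpoints, NIHSS, mRS, EQ-5D, laboratory panel) on the calendar date, whether or not study drug was stopped and whether or not an adverse event is still open.
- Open adverse events are followed separately to resolution or stability under Section 15.
- The actual assessment date is recorded.
- Values taken after the window because of the present wording are not used as the Day 90 value. This can be stated in the SAP, together with how a missing in-window score is handled.

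The cost is a one-sentence amendment and a note to sites. It needs no visit beyond those Section 7.6 already requires, and no change to treatment.

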#### **7.5.4 Loss to follow-up**

Investigators should try their best to keep contact with every patient, making sure the reason of loss to follow-up and their health situation. All CRFs of missed patients should be recorded until the last follow-up visit.

#### **7.6 Quit from study**

Those who quit the study should not be included again. The randomization number and study drugs of this subject should not be used again. Randomized patients must not be replaced. Investigators should confirm the withdrawal along with the monitoring committee. Subjects who were randomized and had one or more doses recorded were required to complete the calendar visits according to the protocol.

## 8. Blood Sample Collection

Blood sample collection refers to serum, plasma and leukocyte (for detailed information, refer to the “collection and management of the biological sample”) that requires to be collected to the corresponding laboratory and transported thereafter with cold-chain to Beijing Tiantan Hospital for centralized storage and analysis. The time of collection should be documented carefully in the CRF.

### 8.1 Collection time, place and volume

Two blood samples per patient need to be collected at the enrollment hospital, at the time points of "within 24 hours after randomization" and "90±7 days after randomization"; 10ml blood was collected each time, half of which is collected using non-anticoagulant blood collection tube and EDTA anticoagulant blood collection tube respectively.

### 8.2 Place and manner of sample processing and storage

Blood sample processing is completed at the enrollment hospital, and the Beijing Tiantan Hospital, Capital Medical University provides standardized processing procedures (shown in the biological sample collection and processing manual) and training. The extracted serum, plasma and leukocytes are stored at -20°C~-80°C at the enrollment hospital after separation, and should be regularly transferred to Beijing Tiantan Hospital, Capital Medical University for centralized storage via cold chain transportation for subsequent testing and analysis.

### 8.3 Disposal of remaining samples

Surplus samples will be destroyed by Beijing Tiantan Hospital, Capital Medical University.

- 1) Samples that have been used and wastes should be destroyed uniformly after sterilization.
- 2) If there is a special need such as repeat tests, samples can be destroyed after appropriate short-term storage.
- 3) Samples that have not been used 15 years after the end of the study follow-up and wastes should be disinfected and destroyed.
- 4) Biological samples prohibited by the written request of the sample provider and wastes should be disinfected and then uniformly destroyed.
- 5) In some other special conditions, such as sample contamination or the discovery of HIV and other viral infected samples, the project leader will be contacted for sample destruction in a timely manner after discovery.
- 6) All samples destruction need subject leader's knowledge and signature is required
- 7) The method of sample destruction is to use pressure steam sterilization, sterilization temperature 121°C, sterilization time 20 minutes, after the treatment of the sample into a special medical garbage bag according to the hospital medical waste treatment;
- 8) All the disposal process of samples should be recorded accordingly, and the operator should fill in the Sample Destruction Record Form.

## 9. Data Collection

Investigators should finish the CRF promptly as instructed by the protocol and make sure those documents are accurate, complete and without delay. The MRI data of all included patients will be collected in the DICOM form with complete sequence information (sequences T1+T2+FLAIR+DWI/ADC+MRA are required, SWI/GRE-T2\* if qualified). Data collected from vascular test, transthoracic echocardiography, 24hrs Holter and lab tests should be uploaded as original photo or in the DICOM form.

## 10. Study Procedure

All subjects should be screened by investigators with a screening table containing the sub-center number. The screening table will be used to analysis representativeness of subjects included in the study in each sub-center.

### 10.1 Screening and enrollment

- Patients meeting the inclusion criteria and not the exclusion criteria should sign the informed consent document.
- Confirm the time of the onset of the initial event
- Perform laboratory tests assessment, including the first emergency routine, emergency renal function (serum creatinine, blood urea nitrogen), emergency liver function (serum transaminase) and emergency blood clotting after onset.
- Perform imaging assessment: brain histology assessment, and/or intracranial artery assessment, and/or extracranial artery assessment. Brain histology assessment includes head CT or MRI for diagnosis and differential diagnosis of TIA and cerebral infarction and possible cerebral infarction model evaluation. Intracranial and extracranial artery assessment examination are used for screening. Intracranial artery assessment examination includes any test of MRA、CTA、DSA. Extracranial artery assessment examination includes any test of neck vascular ultrasound, CEMRA, CTA on the aortic arch, DSA;

**Note:** If a patient is found to be arterial stenosis only by assessing the intracranial arteries and meets the inclusion criteria, he/she can be enrolled without extracranial artery assessment examination. Similarly, if a patient is found to be arterial stenosis only by assessing the extracranial arteries and meets the inclusion criteria, he/she can be enrolled without intracranial artery assessment examination.

(As these radiological tests are recommended as routine tests for ischemic stroke and TIA patients, these examinations will be at patients' own expense)

A thorough explanation of the information of the study will be outlined and shown by the investigators in the written material.

### 10.2 Day of Randomization

- Record basic demographic information, medical and medication history and physical examination of subjects
- Conduct ABCD score (for TIA patients), EQ-5D score and neurological examination (including mRS and NIHSS).
- Apply 12-lead electrocardiogram (ECG) to rule out atrial fibrillation, sick sinus syndrome and second or third degree atrioventricular block.
- Subjects obtain random code, and receive a drug box (for phase 1) in accordance to the

randomization number to supply the study drug used from day 1 to day 21. Study drugs should be taken as soon as the randomization is finished (within 1 hour after randomization). Instructions for taking the first study drug should be given by the investigator. (The first dose includes the total dose of medication taken by the patient after the onset of illness, taken in the ambulance and emergency room, and taken after admission to the hospital).

- Fasting laboratory tests should be completed within 24 hours after randomization (Including routine blood counts, biochemical panel [hepatic function, kidney function, blood lipid, creatine kinase], glycated hemoglobin, homocysteine, coagulation function). Fasting venous blood sample should be collected at the same time, and serum, plasma and white blood cells should be extracted and stored separately (Instructions are listed in the biological sample collection handbook). If not, 72 hours after randomization is the final deadline.
- Complete the initial diagnosis of the initial event for subjects.
- High-resolution MRI of intracranial arteries (high-resolution MRI subgroup only): need to be done within 24 hours of randomization completion.

